### Statistical methods and data management

Data management, including monitoring, is performed by the study sponsor to ensure data completeness and accuracy. Additionally, a noninvestigator physician Steering Committee performs data review and adjudication. As part of standard practice for IDE studies, the FDA conducts occasional audits of the study conduct, data collection, and data management. Study investigators will have access to the data after study closure and will be offered the opportunity to participate as authors on publications. Electronic data capture with appropriate security protocols is used to ensure participant confidentiality during and after the study closure.

Statistical analyses will be performed using a significance level of *p* = 0.05, unless otherwise specified, and 95% confidence intervals will be computed. Interim analyses for the primary endpoint will occur when all randomized participants complete the 24-week visit; results of that analysis will be submitted for publication. Analyses of the long-term follow-ups will be reported after study closure.

#### Sample size

Noninferiority of the VAS score during burst compared with tonic stimulation was assumed to be within a window of 7.5 mm on the 100-mm VAS. Based on earlier reports, the standard deviation of the difference between tonic and burst stimulation VAS scores was assumed to be 18.4 mm. With a type I error rate of 0.05, a minimum sample of 76 participants was required to achieve 80% power to show noninferiority between the two stimulation modes.

Previous studies indicate that approximately 29% of subjects trialed with tonic stimulation do not receive a permanent implant and an additional 20% of subjects may be lost to attrition by the 6-month visit [18]. Screen failure rates were originally estimated to be at 15%, but after the first 6 months of enrollment the screen failure rate was amended to 22%. Total enrollment communicated with the regulatory bodies was 173 to account for screen failures, trial evaluation failures, and normal attrition [76/.71 = 108/.80 = 135/.78 = 173 (rounding up at each step)].

The noninferiority margin was set to preserve at least 50% of the expected effect [19, 20]. Assuming, based upon enrollment criteria and past literature [21], the average baseline pain is approximately 75 mm, a 30% improvement in VAS score would be 23 mm. The 7.5-mm margin on the VAS scale would preserve approximately 77% of the effect and would, therefore, be an appropriate margin.

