### Trial design

The study consists of two distinct phases: (1) a 24-week controlled (cross-over) phase during which participants are randomly assigned to one of two treatment sequences of tonic and burst stimulation, each for 12 weeks and (2) an open-label phase during which participants may use either waveform (see Figs. 1 and 2). With guidance from the FDA, the study employs enrichment strategies aimed at decreasing variability and assessing the efficacy of burst compared to an approved SCS waveform. As such, participants are limited to those who achieve adequate pain relief during a traditional tonic stimulation trial evaluation; all participants use both waveforms in a within-subject cross-over design.

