#### Primary analysis

The primary effectiveness analysis is the 12-week noninferiority of the within-subject difference between tonic and burst stimulation for the mean daily overall VAS score calculated from the diary. The primary analysis will be conducted using the intention-to-treat population to include data recorded at the 12- and 24-week visits for all randomized participants, except as noted below. Missing data will be imputed using the hot-deck or last-observation-carried-forward method, as appropriate. If participants increase their pain medications during the first 24 weeks of the study, assessment of the effect of the therapy mode on pain will be confounded by the influence of additional pain medications. Thus, participants who increase pain medication (other than acetaminophen) after randomization will be considered treatment failures for the interval during which the increase occurred, and that participant’s baseline mean daily VAS score will be used for that interval in the analysis. A Z-statistic compared with the standard normal distribution will test the null hypothesis that the within-subject difference for the mean overall VAS score is less than or equal to 7.5 mm.

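### The stated 76 participants and 80% power do not follow from the stated SD of the difference (18.4 mm) and margin (7.5 mm); with a true difference of 0, 76 gives about 97% or 94% power

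*Protocol article*

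**What the plan says.** The Sample size section of the protocol article gives every main input. The noninferiority difference "was assumed to be within a window of 7.5 mm on the 100-mm VAS". On variability, "the standard deviation of the difference between tonic and burst stimulation VAS scores was assumed to be 18.4 mm". The error rate is given as "With a type I error rate of 0.05", without saying whether it is one- or two-sided. From these the article concludes that "a minimum sample of 76 participants was required to achieve 80% power to show noninferiority between the two stimulation modes".

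The design is paired: under Trial design, "all participants use both waveforms in a within-subject cross-over design", and under Primary analysis, "The primary effectiveness analysis is the 12-week noninferiority of the within-subject difference between tonic and burst stimulation". The test is also named there: "A Z-statistic compared with the standard normal distribution will test the null hypothesis". The general statistical paragraph adds that "95% confidence intervals will be computed", which is the only other hint on sidedness.

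The 76 is then inflated for failed trial stimulation, attrition and screen failure, in the chain 76 → 108 → 135 → 173. The article reports 173 as the enrolment total given to regulators.

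**The concern.** In a cross-over each participant contributes one difference, so an SD of the difference goes straight into the one-sample formula. Done that way, the stated inputs lead to roughly half of 76, or to far more than 80% power at 76. The stated number, power and SD therefore cannot all be right unless some further assumption was made that the article does not give.

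The explanations have different consequences. If the label on 18.4 mm is right and no difference was assumed, the trial has ample power and could carry a stricter alpha. If 18.4 mm is a per-period SD, the power is 80% at one-sided 0.05 and about 70% at one-sided 0.025. A reader of the article cannot tell which applies, and the whole enrolment chain rests on the 76.

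**Working it through.** **Inputs from the Sample size section:** margin m = 7.5 mm; SD of the difference s = 18.4 mm; type I error 0.05; power 80%; n = 76. **Assumed here because not stated:** true difference 0, with both one-sided 0.05 and one-sided 0.025 tried.

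**Step 1. Attempt to reproduce 76 as written.** Paired noninferiority: n = (z₁₋α + z₀.₈₀)² · s² / m².

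- One-sided 0.05: (1.645 + 0.842)² × 18.4² / 7.5² = 37.2, so 38; with the t distribution, 39.
- One-sided 0.025: (1.960 + 0.842)² × 18.4² / 7.5² = 47.2, so 48; with the t distribution, 50.

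Neither gives 76. Reading the window as two-sided equivalence (two one-sided tests, paired) gives 52 at 0.05 per side or 64 at 0.025 per side. Attrition cannot account for the gap, because it is applied after the 76.

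**Step 2. Power at n = 76 as written.** Standard error = 18.4/√76 = 2.11 mm, and 7.5/2.11 = 3.55.

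| One-sided α | Power (z) | Power (t) |
|---|---|---|
| 0.05 | Φ(3.55 − 1.645) = 97.2% | 97.0% |
| 0.025 | Φ(3.55 − 1.960) = 94.4% | 93.9% |

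**Step 3. What does recover 76 with 80% power.**

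- *18.4 mm as a per-period within-subject SD.* The SD of the difference is then 18.4 × √2 = 26.0 mm. At one-sided 0.05 the formula gives 74.4, so 75 by z. A t-based calculation with equal sequence groups gives 76 in total, with 80.1% power. At one-sided 0.025 the power at 76 is about 70% (69.8%), and 98 would be needed.
- *Two-sample formula with 18.4 mm as the SD in each group.* n per group = 2 × 37.2 = 74.4, so 75 by z and 76 by t (power 80.4%). Here 76 is a count per group.
- *Label correct, non-zero true difference.* Solving m − s(z₁₋α + z₀.₈₀)/√76 for the difference gives 7.5 − 5.25 = 2.25 mm against burst at one-sided 0.05, or 7.5 − 5.91 = 1.59 mm at one-sided 0.025.

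**Step 4. Inflation chain.** 76/0.71 = 107.04, up to 108; 108/0.80 = 135; 135/0.78 = 173.08, which rounds up to 174. The reported 173 is ordinary rounding at the last step.

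**The case against.** The strongest reply is that a true difference of 0 is supplied by the check and not by the article. If the sponsor planned for burst to be slightly worse, 76 and 80% stand with the 18.4 mm label intact. The Background lends some colour to this, since it describes earlier pain results as close, with a marginal shortfall for burst. A condensed article may also leave an assumed difference to the full protocol. This part of the reply stands: the 38–39 and 97% are conditional, and a small planned disadvantage must be listed among the explanations. It is not confirmed either. The Background also says burst may surpass tonic in some patients, and the Objectives include showing that burst is superior.

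A second reply is that the match at 76 does not identify the mistake. That also stands. The exact match needs a t-based calculation, whereas the planned test is a Z test and z gives 75. A two-sample per-group formula lands on 76 as well. A reader might infer that 18.4 mm is certainly mislabelled; the documents do not establish that.

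A third reply is that nothing is lost at the stated error rate. Read as one-sided 0.05, none of the three explanations puts the paired test with 76 participants below 80%. The 70% figure needs both an SD of the difference of 26.0 mm and one-sided 0.025. The 95% intervals leave that level open, but the article does not state it for this test.

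The appeal to condensation does not remove the point. The article does not merely omit a detail: the SD, margin, power and sample size that it does state do not agree with each other without an addition.

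**Conclusion.** The sample-size statement is not reproducible from its own inputs. Conditional on a true difference of 0 and the SD as labelled, 80% power needs 38–39 participants (one-sided 0.05) or 48–50 (one-sided 0.025), and 76 gives about 97% or 94%. The mismatch holds under either sidedness and under z or t. Which element is at fault cannot be settled from the article.

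Two stronger conclusions are tempting. One is that the trial needs only about 39 participants and recruits twice too many; that requires the label, the zero difference and one-sided 0.05 all to hold, and the last two are not stated. The other is that the trial is underpowered; that requires a different SD and a stricter alpha than the article gives. Nor can one say that the regulator was left unsure, because the full protocol submitted to it is not shown. The finding is a reporting inconsistency in the enrolment justification.

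The rounding slip at the last inflation step is one participant and trivial.

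**What to change.** Check the source of the 18.4 mm and restate the Sample size paragraph with:

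- what the SD refers to (within-subject difference, per-period within-subject, or per-group);
- the formula used, and whether 76 is a total or a per-group count;
- the sidedness of the 0.05;
- the assumed true difference;
- the power that 76 completers then give.

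For example, if the label is right and the assumed difference is 0, state 97% at one-sided 0.05 or 94% at one-sided 0.025. If 18.4 mm is a per-period within-subject SD, give the SD of the difference as about 26.0 mm and state 80% at one-sided 0.05 or about 70% at one-sided 0.025. If a disadvantage for burst was planned, state its size.

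Correct the remark that every step was rounded up. Leave 173 as it is, since it is reported as the figure given to regulators. The cost is one search for the source of the SD and the rewording of one paragraph; enrolment need not change.

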#### Carryover estimations

Prior to analysis, measures will be inspected for carryover effects that may be present as a function of time and/or the order of therapy delivery. Carryover effects will be estimated using the within-subject sums of the score from week 1 to week 12 and from week 12 to week 24. An independent two-sided *t* test will test the null hypothesis of equal within-subject sums between the two sequence groups tonic/burst stimulation and burst/tonic stimulation. If the null hypothesis is not rejected at the 0.10 level, then the potential carryover effects are considered negligible. If the null hypothesis is rejected, the subsequent analysis will be carried out on the first-period data only.

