**Fig. 2 Fig2:**
[figure not shown]
Standard Protocol Items: Recommendations for Interventional Trials (SPIRIT) figure

At up to 20 centers in the U.S., Institutional Review Board (IRB) approval is obtained (refer to its “Declarations” page), and eligible enrolled participants undergo additional screening and participate in a standard SCS trial evaluation using tonic stimulation. Those with a successful SCS trial evaluation are implanted with the Prodigy™ neurostimulation system (St. Jude Medical, Plano, TX, USA) that can deliver both burst and tonic waveforms. Lead position for the permanent system is determined by placement for optimum paresthesia coverage during the tonic stimulation trial evaluation. After a 2–3 week surgical recovery period, participants with the permanent system are randomized to receive one of the two treatment sequences over the subsequent 24 weeks.

During the control phase, participants use one waveform for 12 weeks then cross over to the other waveform for the remaining 12 weeks. Participants are randomly assigned (1:1) at each study site using computer-generated assignment to receive 12 weeks of tonic stimulation followed by 12 weeks of burst stimulation, or 12 weeks of burst stimulation followed by 12 weeks of tonic stimulation. Participants in both groups complete assessments at 6, 12, 18, and 24 weeks after randomization.

To enhance participant compliance with the study protocol, a washout period was not employed when participants crossed over. This decision was based on previous reports suggesting that 25–80% of patients may fail to comply with the study protocol when asked to undergo periods without stimulation [9, 10]. Assessments occur at a minimum of 6 weeks after changing stimulation modes, which is adequate time to ensure that any after-effects of the previous therapy will not influence the assessment of the current therapy [11, 12].

During the open-label phase of the study, participants attend study visits for assessment every 6 months for up to 2 years post randomization. Perceptible differences in paresthesia between the two waveforms are likely, thus neither patients nor investigators are blinded to treatment sequence.

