Furthermore, participants with marked depressive symptoms are excluded from eligibility in this study. Affective and functional dimensions are reflected in patients’ impression of change – even when a reduction in pain intensity may be considered clinically minimal [22]. Affective disruptions commonly associated with pain may also interfere with an accurate assessment of changes in pain intensity. Our study is intended to provide a comparative inspection of pain during burst and tonic stimulation that is largely independent of affective improvements that may indirectly influence participant’s assessment of therapy. We recognize that a minority of chronic pain patients, as few as 14% by some accounts, present without significant depressive symptoms [23, 24]. Excluding participants with depressive symptoms is not expected to limit generalizability, however, because the population included in this design is expected to provide a conservative estimate of pain relief during stimulation. Any direct or indirect benefits to affective function conferred by burst stimulation would be expected to be additive, not exclusive, to the effects on pain. Thus, the results of this study would be expected to approximate, possibly to a lesser degree, the efficacy of burst stimulation for general clinic populations.

In contrast, our sample of participants with minimal affective disruption is likely to create a “floor effect” whereby comparative improvements in psychosocial outcomes for burst versus tonic stimulation are unlikely to be detectable. Early evidence indicates that some psychosocial domains may be differentially affected during burst stimulation compared to tonic stimulation [5]; future studies will be needed to target this aspect of the therapy.

The cross-over design also imposes some limitations upon the hypotheses that can be addressed with these results. First, the presence of any carryover effects, although not expected, may limit our analysis by reducing the treatment window to the first 3-month period – thus leading to a between-subject comparison. Second, we will be unable to statistically assess changes in pain across time without losing the benefits of the within-subject design. Much of the literature for chronic pain treatments focuses on a calculated change in pain from baseline to follow-up. Our study design is not intended for such an analysis and any inspection of the similar results in our study will lead to limited conclusions, at best.

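### Letting a carryover pre-test choose between the crossover and a first-period-only analysis raises the false-noninferiority rate above nominal and, when it fires, discards half the outcome data

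*Protocol article*

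**What the plan says.** Under Carryover estimations, each participant's scores are summed over the two 12-week periods. The sums are compared between sequences with a two-sided independent t test at 0.10. If the test does not reject, carryover is treated as negligible. Otherwise "If the null hypothesis is rejected, the subsequent analysis will be carried out on the first-period data only".

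The Discussion accepts the consequence: "the presence of any carryover effects, although not expected, may limit our analysis by reducing the treatment window to the first 3-month period", leaving a between-subject comparison. Trial design states that there is no washout and describes the minimum of 6 weeks on the new mode as "adequate time to ensure that any after-effects of the previous therapy will not influence the assessment of the current therapy".

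Under Sample size the trial is sized on the within-subject difference: "the standard deviation of the difference between tonic and burst stimulation VAS scores was assumed to be 18.4 mm". The article gives no power for a first-period analysis and no adjustment of the error rate for the two-stage choice.

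**The concern.** The pre-test statistic is period 1 plus period 2, and the fallback statistic is period 1 alone. They share data, so a chance rejection of the first selects trials in which the second is also far from its expected value. Testing the first-period contrast at its usual level after that selection is invalid.

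The pre-test is itself a between-subject comparison. It has little power against a carryover that matters, yet by construction it fires in 10% of trials with none. What is at stake is the confirmatory noninferiority conclusion intended to support regulatory approval. The damage cannot be repaired once the branch has been chosen from the data.

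**Working it through.** **Inputs from the article.** Margin 7.5 mm; SD of the tonic–burst difference 18.4 mm; type I error 0.05; 76 participants for 80% power; 1:1 allocation, hence 38 per sequence; pre-test level 0.10. The primary test is described only as "A Z-statistic compared with the standard normal distribution will test the null hypothesis", so its sidedness is not stated. The single-period SD (equivalently the between-period correlation ρ) is not given and is varied below.

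**1. The plan's own sample size.** With a true difference of 0, the paired formula is n = ((z_α + z_β) × SD / margin)².
- One-sided 0.05: ((1.645 + 0.842) × 18.4 / 7.5)² = 37.2, so 38.
- One-sided 0.025: 47.2, so 48.

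The stated 76 equals 2 × 38 and is reached only at one-sided 0.05. That level is used as the main reading; 0.025 is shown alongside.

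**2. Correlation of the two statistics.** SD of the difference = SD × √(2(1 − ρ)), so ρ = 1 − 18.4²/(2 × SD²). SD 18 mm gives ρ = 0.48 and SD 25 mm gives ρ = 0.73. The correlation between the sum contrast and the period-1 contrast is √((1 + ρ)/2) = 0.86 and 0.93. It is 0.71 even at ρ = 0.

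**3. Type I error, no carryover, true difference at the margin.** Overall rate ≈ 0.90 × 0.05 + 0.10 × (rate given a pre-test rejection). A bivariate normal calculation gives conditional rates of 0.29 (SD 18) and 0.35 (SD 25):
- SD 18: 0.045 + 0.029 = 7.4%
- SD 25: 0.045 + 0.035 = 8.0%

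Simulating the whole rule with estimated variances gives slightly higher values, about 7.5–8.3% over the same SD range. Over a wider range of ρ (100,000 trials per row for the error rates; first-period power calculated at one-sided 0.05):

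| ρ | Single-period SD (mm) | False NI given rejection, 0.05 | Overall, nominal 0.05 | Overall, nominal 0.025 | First-period power |
|---|---|---|---|---|---|
| 0 | 13.0 | 21% | 6.8% | 3.8% | 81% |
| 0.3 | 15.6 | 25% | 7.3% | 4.1% | 68% |
| 0.5 | 18.4 | 30% | 7.7% | 4.4% | 55% |
| 0.7 | 23.8 | 35% | 8.3% | 4.6% | 39% |
| 0.8 | 29.1 | 38% | 8.4% | 4.8% | 30% |

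The crossover analysis without the pre-test gives about 5.2% and 2.7%. That small excess comes from using a Z reference with an estimated SD.

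**4. Power at a true difference of 0, one-sided 0.05.**
- Crossover: Φ(7.5/(18.4/√76) − 1.645) = Φ(1.91) = 97%.
- First period only: Φ(7.5/(SD × √(2/38)) − 1.645) = 57% at SD 18 and 37% at SD 25.
- At ρ = 0.5, 80% first-period power needs 75 per sequence, 150 in all.

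**5. Power of the pre-test.** Its standard error is √(2 × SD² × (1 + ρ)) × √(2/38) = 7.1 mm (SD 18) to 10.7 mm (SD 25). Against a 7.5 mm carryover at two-sided 0.10, power is 28% and 18%.

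**6. If carryover is real.** Take 7.5 mm that worsens tonic after burst, with the true difference at the margin. The crossover estimate shifts by 7.5/2 = 3.75 mm in burst's favor. False noninferiority is about 54% without the pre-test and about 39–45% with it.

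**The case against.** Several points on the other side have substance.

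- **Sidedness.** If the primary test is run at one-sided 0.025, the overall rate stays below 0.05. It still exceeds its own nominal level, and the stated 76 does not come from 0.025.
- **Average power.** Over both branches, power falls only from 97% to about 92–94% at one-sided 0.05, above the 80% target. This stands: the severe loss is confined to the triggered branch, and it eases as ρ approaches 0.
- **Sample size.** The 76 is before attrition; 76/0.80 = 95 would be randomized and all are to be analyzed with imputation. With about 47 per sequence, first-period power is about 42–64% for SD 18–25 mm, still well short of the crossover.
- **Meaning of the sums.** They may cover all four control-phase visits. On that reading, with an assumed within-period correlation of 0.6–0.85, the overall rate is 7.2–8.1%, little different.
- **Disclosure.** The Discussion admits the loss of the within-subject comparison. It does not mention the error inflation.
- **Protection against carryover.** This is the strongest point. There is no washout, and if carryover favors burst the pre-test lowers the false-noninferiority rate: 54% to about 39–45% at 7.5 mm, and 96% to 32–58% at 15 mm. So dropping it is a trade-off. But a procedure that still errs about 40% of the time under a carryover equal to the margin does not control error, and it costs validity when carryover is absent, which is what the article expects.

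**Conclusion.** Wrong as written. The rule is fully specified in the article, so this is not a detail left to an unseen analysis plan. With no carryover, it raises the false-noninferiority rate to about 1.4–1.7 times nominal at one-sided 0.05 (6.8–8.4% across ρ from 0 to 0.8), and to 3.8–4.8% at nominal 0.025. The excess appears at every correlation tried, including zero. In the one trial in ten where the pre-test fires by chance, the primary conclusion rests on a test for which the trial was not sized.

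These figures assume normal data, 38 per sequence, the stated 18.4 mm SD of the difference, and sums taken over one score per period. The single-period SD is an assumption, and first-period power is the result most sensitive to it.

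**What to change.** Delete the conditional step. State that the primary noninferiority test is the period-adjusted crossover analysis of the week-12 and week-24 scores, whatever the carryover comparison shows. In simulation under the same assumptions, with a t reference, that analysis holds its level (4.9–5.0% at nominal 0.05) with 97% power at 76 participants.

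Report as sensitivity analyses only: the sequence (carryover) contrast with its confidence interval, and the first-period burst-minus-tonic difference with its interval. State that a real unequal carryover would bias the crossover estimate by about half its size, so that readers can judge the primary result against those two estimates.

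The cost is a wording change to the protocol and analysis plan, with no change to visits or sample size. The price is that unequal carryover would be displayed but would not alter the primary test. The trial is described as ongoing, so the change should be made and dated before outcome data are analyzed.
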